## Abstract

**Background:**

For more responsive care provision for motor neuron disease and caregivers, a digital system called Telehealth in MND-Care (TiM-C) was created. TiM-C sends regular symptom questionnaires to users; their responses are sent to health care professionals (HCPs). To enable people with motor neuron disease to participate in research studies more easily, a parallel platform was developed from TiM-C, called Telehealth in MND-Research (TiM-R). TiM-R can advertise studies, collect data, and make them available to MND researchers.

**Objective:**

This study has 4 work packages (WPs) to facilitate service approval, codevelop the TiM systems, and evaluate the service. Each WP aims to understand (1) what helps and hinders the approval of the TiM-C system as a National Health Service; (2) what aspects of MND care and research are currently unmet and can be addressed through the TiM-C and TiM-R systems; (3) how TiM-C influences MND care, from the perspective of people with motor neuron disease, their caregivers, and HCPs; and (4) the costs and benefits associated with TiM-C.

**Methods:**

WP1 will use semistructured interviews with 10-15 people involved in the approval of TiM-C to understand the barriers and facilitators to governance processes. WP2 will use individual and group interviews with 25-35 users (people with motor neuron disease, caregivers, HCPs, MND researchers, and industry) of TiM-C and TiM-R to understand the current unmet needs of these user groups and how TiM services can be developed to meet these needs. WP3 will use a process evaluation involving 5 elements; local context, engagement, user experiences, service impact, and mechanisms of action. A range of methods, including audits, analysis of routine data, questionnaires, interviews, and observations will be used with people with motor neuron disease, caregivers, and HCPs, both those using the system and those who declined the service when invited. WP4 will use data collected through the process evaluation and known costs to conduct a cost-consequence and budget impact analysis to explore the cost-benefit of the TiM-C service. Most data collected will be qualitative, with thematic and framework analysis used to develop themes from transcripts and observations. Descriptive statistics or *t* tests and chi-square tests will be used to describe and analyze quantitative data.

**Results:**

This study has received ethical approval and has begun recruitment in 1 site. Further, 13 specialist MND centers will adopt TiM-C and the TIME study, beginning in July 2024. The study will conclude in November 2026 and a final report will be produced 3 months after the completion date.

**Conclusions:**

This study will facilitate the implementation and development of TiM-C and TiM-R and fully evaluate the TiM-C service, enabling informed decision-making among health care providers regarding continued involvement and contribute to the wider literature relating to how technology-enabled care services can affect clinical care.

**International Registered Report Identifier (IRRID):**

DERR1-10.2196/57685

## Introduction

Motor neuron disease (MND) is an incurable disease, that causes progressive weakness of muscles involving the limbs, speech, and swallowing, leading to progressive disability and eventual respiratory failure. In the United Kingdom, there are approximately 5000 people with MND at any one time [1]. The average life expectancy following diagnosis is 2 to 3 years but the course of MND can vary from only a few months to over 10 years. The distress and burden of the disease affects people with MND, their family, and caregivers and the relenting progression of disability causes social, emotional, and financial strain [2,3].

In the United Kingdom, multidisciplinary teams (MDTs) deliver specialist MND care through MND Care Centers or care networks across the country. Expert health care professionals (HCPs) monitor symptoms and offer interventions such as Riluzole, which can improve survival by approximately 2 to 3 months [4], gastrostomy feeding to promote good nutrition [4], or treatment of respiratory failure with noninvasive ventilation, which improves both quality of life and life-expectancy [5]. Attendance at specialist MND clinics has been reported to improve survival independent of these other interventions [6,7]. Traditionally, clinics are held at regular fixed intervals, approximately 3 months apart.

Despite the potential benefits of MDT care, this model is not always sufficiently responsive to the needs of patients because these can change rapidly, and therefore, can require people with MND and their families to undertake progressively more difficult journeys to the clinic at a time predicted by the clinician at their last meeting. Given the burden associated with traveling to the clinic, it is important that visits occur when they are most needed. Conversely, some people with MND whose needs may not change considerably over time, may not benefit from a clinic appointment every 3 months.

To supplement traditional care for people with MND and their caregivers, and provide greater information on symptoms for the MDT, the Telehealth in MND-Care on MyPathway system (herein referred to as TiM-C) was codeveloped with people with MND, caregivers, and HCPs. TiM-C is software that enables people with MND and their caregivers to report their progress and symptoms to the hospital MDT from their homes using an app or via the online website [8] (TiM-C). Users are regularly asked to complete a variety of symptom questionnaires (eg, appetite, weight, functional rating, breathing, and mental health), answers to which are securely sent to the clinical portal. An initial evaluation in one center found TiM-C to be easy to use, even for those with significant disabilities, acceptable, and low in burden, taking approximately 5 minutes per week to complete. Around 85% of people with MND would recommend TiM-C to others and 95% would use TiM-C if they could not travel to the clinic. HCPs also found it accurate and easy to use [9,10]. However, additional research is needed to understand how best to implement TiM-C in MND centers, further user needs, the impact of the service, and the costs of the system. TiM-C is currently being adopted as a clinical service within 14 MND specialist centers across the United Kingdom.

In addition to supporting clinical care, this type of remote monitoring is a useful method for research data collection [11,12]. Therefore, a second system called Telehealth in MND-Research (TiM-R; Figure 1) is being adapted from TiM-C to decrease the burden of MND research and enable people with MND to participate in studies regardless of where they live. However, it is important to codevelop technological systems to best meet the needs of end users [12,13] and research is required to ensure TiM-R is feasible and acceptable for people with MND, caregivers, HCPs, and MND researchers before this is launched in Summer 2024.

The aim of this study is to create an approval strategy alongside information governance experts, further develop TiM-C and TiM-R alongside end users, and understand the effects on clinical practice and cost of the TiM-C clinical service. The following research questions will be answered:

From the perspective of individuals involved in the approval of National Health Service (NHS) services, what are the barriers and facilitators of approving TiM-C at scale?What are the unmet needs of people with MND, their caregivers, HCPs, MND researchers, and industry?How can TiM-C and TiM-R be developed to support end user needs?Does the use of the TiM-C service result in better MDT care for people with MND and their caregivers?What are the costs associated with the TiM-C service and how do they affect health care expenditure?

**Figure 1 figure1:**
[figure not shown]
Overview of how TiM-R links patients to research. MND: motor neuron disease; NHS: National Health Service; TiM-R: telehealth in MND-research.

## Methods

### Design

The design of this project was based upon multiple frameworks and guidelines, which have helped develop a logic model, consider outcomes, and data collection methods. These include the MRC framework for the development and evaluation of complex interventions [14], National Institute for Health and Care Excellence Evidence Standards Framework [15], Person-based approach to intervention development [13], and Non-adoption, Abandonment, Scale-up, Spread, and Sustainability (NASSS) [16]. A total of 14 sites will collect data, however, some work packages (WPs) will only use a subset of sites (eg, WP1 only collects data from 5). The project has 4, interconnected WPs, which answer the research questions above:

Governance approval strategy development (research question 1)TiM-C and TiM-R codevelopment (research questions 2 and 3)TiM-C process evaluation (research question 4)TiM-C economic evaluation (research question 5)

Through the NASSS framework and the collection of other data in the 2nd and 3rd work packages (described below), we will collect information that can be used to identify barriers that affect TiM-C and TiM-R implementation and use. Throughout the study, using an implementation science lens, we will address identified barriers to facilitate the uptake of the TiM system, using methods suggested by Cane et al [17]. We will document any adaptations made to our governance approval strategy or the TiM intervention.

To reduce the number of under-served groups within this project, the research team will aim to involve a diverse range of participants throughout the entirety of this study and overcome known barriers to participation [18]. This will include remote research activities to reduce the need to travel, support for caregivers to enable participation, and continual data monitoring to ensure representative inclusion of different ages and genders.

Each of the 14 sites involved in this study will be given permission to mildly modify research activities to enable people with different abilities or circumstances, who meet the eligibility criteria, to participate in any and all parts of the study they want to. For example, modifying consent or data collection procedures to enable the participation of people with MND and caregivers who are physically unable to complete documents, or questions being shared ahead of an interview to allow participants who have difficulty communicating time to prepare recorded answers.

### Development of a Governance Approval Strategy (WP1)

This WP will use qualitative research to understand and assess the barriers and facilitators of successful technology approval. The research question in this work package will be addressed using a qualitative approach because there is a dearth of information available on which aspects help and hinder technology governance approval in MND care within the NHS [19]. Therefore, the semistructured interviews with individuals involved in the approval process of the TiM-C system within NHS organizations will provide rich data on this issue [20].

Convenience sampling will be used to recruit 10-15 individuals involved in the approval process of TiM-C (eg, governance, ICT, and data security staff) within 5 NHS organizations (out of the 14 using TiM-C). Semistructured interviews will be conducted using video-conferencing software (in line with participant preferences and permissions) or telephone. The interviews will last approximately 30-60 minutes in duration and be conducted by members of the research team.

The interviews will begin with general, open-ended questions relating to the participant’s experience within their work role, and how they were involved in the approval process of TiM-C. Specific questions will explore what aspects of the approval process went smoothly and what factors they believe contributed to this. Further questions will relate to aspects of the approval process that hindered progress and how these may be overcome in the future. The interview schedule is informed by the NASSS framework, combined with the Complexity Assessment Toolkit (NASSS-CAT) [16] to help identify areas of complexity within NHS organizations.

Interviews will be audio-recorded and transcribed verbatim for analysis. All identifiable information will be removed during transcription with a pseudonym replacing the participant’s name. The research team will conduct a framework analysis using NVivo [21]. The analysis will focus on semantic (as opposed to latent) meanings within the transcripts. The information gained from this WP will be used to inform a toolkit that provides suggestions for future health care interventions aiming to become clinically adopted services within the NHS. This toolkit will be freely available and provide suggestions gained from the governance experts interviewed to decrease the current lengthy process of service adoption.

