## Discussion

### Principal Findings

This study will collect data relating to NHS clinical approvals, TiM-C and TiM-R development, and evaluate the TiM-C service. The project will open approximately 14 sites to recruit to all WPs. The study is due to be completed in November 2026, and the final report will be produced within 3 months of the study closing. However, we will also separately disseminate the results for each WP. We anticipate that the data from WP1 will enable the development of a toolkit to aid the approval process of future health care interventions in the NHS, which will be disseminated through a publication and publicly available website. This responds to our group’s collaboration with multiple industry partners who describe significant delays in governance approval processes. Findings from WP2 will primarily inform the refinement of TiM-C and TiM-R, but could also be useful for future researchers who wish to develop innovative digital services for people with long-term conditions. We will publish this through 2 academic publications.

WP3 and WP4 will collect data relating to the current provision of MND services and the effect of TiM-C on this provision. We anticipate that this will enable greater conclusions to be drawn relating to the benefits and consequences of the TiM-C service, whilst also enabling the testing of our program theory and logic model. As per the MRC’s guidelines for complex intervention development [14], we will explore whether to further explore implementation and effectiveness depending on the results of the process evaluation. Alongside stakeholders, we will publish this work academically but also work with wider groups (eg, NHS decision makers, policy groups, and charities) to increase the impact of this work.

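### WP1 asks what hinders approval of TiM-C, but its sampling rule leaves slow or stalled approvals to chance and does not reach organizations outside the 14

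*Protocol article*

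**What the plan says.** The Objective in the Abstract has WP1 find out "what helps and hinders the approval of the TiM-C system as a National Health Service". The matching research question in the Introduction is "what are the barriers and facilitators of approving TiM-C at scale".

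The sampling rule is in the Methods section on WP1: "Convenience sampling will be used to recruit 10-15 individuals involved in the approval process of TiM-C", such as governance, ICT and data security staff, "within 5 NHS organizations (out of the 14 using TiM-C"). The Design section agrees: "some work packages (WPs) will only use a subset of sites (eg, WP1 only collects data from 5").

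The interviews cover what went smoothly and also the difficulties: "Further questions will relate to aspects of the approval process that hindered progress and how these may be overcome in the future". On use of the results: "The information gained from this WP will be used to inform a toolkit that provides suggestions for future health care interventions" that seek NHS adoption. Principal Findings gives the motive: industry partners report "significant delays in governance approval processes".

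**The concern.** The study wants to learn about obstacles to approval, yet the stated frame is defined by use of TiM-C, which is what approval leads to. Within that frame the only stated selection method is convenience, and nothing directs it toward organizations where approval was difficult.

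Two things could be lost. An obstacle that ended an approval cannot be reported by an organization that is not in the frame. An obstacle that caused long delay is reported only if a slow organization happens to be among the 5. The toolkit is meant for services that expect a long or uncertain approval, so a sample weighted toward easy approvals would serve its users least where they most need help.

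**Working it through.** No sample-size or error-rate formula applies to a qualitative work package, so the check compares the aim with the frame.

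**Counts**
- Sites (Results in the Abstract): 1 already recruiting + 13 to adopt from July 2024 = 14, which matches the 14 in the WP1 section.
- Organizations sampled: 5/14 = 36%. The other 14 - 5 = 9 contribute no WP1 interview.
- Interviews per organization if spread evenly: 10/5 = 2 to 15/5 = 3. With so few per site, the range of approval experience depends mainly on which 5 organizations are included.

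**Does any other text widen the frame?**
- The eligibility textbox under Participants has no separate criteria for governance staff, so it adds no organizations.
- The Abstract says that WP3 includes people who declined the service when invited. These are individual patients, caregivers and professionals, not organizations that withheld approval.
- Limitations discusses only the lack of a randomized design.
- No section provides for an organization where approval was refused, withdrawn or stalled.

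**Who is inside the 14?**
- The WP1 section describes the 14 as users of TiM-C.
- The Abstract, the Introduction and the Results section describe centers that will adopt it, are adopting it, or are being set up.
- Read together, the 14 are the participating centers, most of them not yet live at the time of writing. A slow or pending center among them can therefore be sampled, but nothing requires it.

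**How do the other work packages sample?**
- WP2 and WP3 state purposive sampling. WP2 also checks during recruitment that no group is being left out.
- WP1 uses an interview guide based on NASSS, a framework whose name begins with non-adoption, but has no comparable provision for organizations.

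**Size.** The article gives no approval dates and no count of organizations that stalled or declined. Any percentage for the chance of missing them would rest on an invented input, so none is given.

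**The case against.** A reader might infer that stalled approvals are excluded by design and that barriers will be learned only from successes. The article does not support that. Most of the 14 were still adopting, so slow and pending sites are within reach, and the interview guide asks directly what hindered progress. Only organizations outside the 14 are left out of the frame.

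A reader might also infer that the 5 organizations are themselves a convenience sample favoring early finishers. The text applies convenience sampling to individuals and does not say how the 5 are chosen. A condensed article may leave that to the full protocol, and its absence alone would not be a finding. A tilt toward early finishers is plausible but not documented.

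Further, the stated motive is mainly delay rather than refusal, no section reports a refusal, and staff who worked through a slow approval can describe it. Exploratory qualitative work also need not be representative or support causal contrasts.

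All of this stands and limits the point. It does not remove it. The frame and the sampling method are stated choices, and neither secures variation in approval experience, which is the thing being studied. Qualitative sampling need not be representative, but it should be rich in information on its question, as the WP2 plan recognizes.

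**Conclusion.** The point holds as a low-cost improvement to the WP1 sampling rule. It does not invalidate the work package. As stated, the rule leaves the inclusion of slow or pending approvals among the 14 to chance and gives no route to organizations outside the 14 that declined or never completed approval. Barriers that ended an approval may go unseen, and the toolkit may lean toward easier approvals.

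The size of any distortion is unknown. The conclusion assumes that the full protocol has no purposive rule for choosing the 5 organizations. The part about organizations outside the 14 matters only if such organizations exist, which the article does not say.

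**What to change.** In the WP1 section, state that the 5 organizations will be selected purposively by time to approval or approval status: for example, at least two of the slowest or still pending at sampling, and at least one of the fastest. Keep 10-15 interviews. Convenience recruitment of staff within the chosen organizations can stay. In the framework analysis, use fast versus slow or pending as a comparison dimension.

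Include a declining organization only where one exists and can be reached. Otherwise, add to Limitations and to the toolkit that its conclusions apply to organizations that adopted or were adopting TiM-C.

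The cost is mainly wording. Staff at slow sites may be harder to recruit. Approval dates must be obtained from the sites if the study team does not already hold them; the article does not say whether it does. A non-adopting organization may need its own local permission, so that step is conditional.

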### TiM-C and TiM-R Development (WP2)

This work package will use a qualitative research design, with semistructured interviews with users of TiM-C and prospective users of TiM-R, including people with MND, caregivers, HCPs, MND researchers, and industry representatives. A qualitative design is most appropriate in order to continue the person-based approach to TiM development [13], and to ensure the intervention remains relevant, acceptable, and feasible, it is important to explore the views of the people who will be interacting with it [22,23]. We will use the information collected throughout this WP to make further refinements to the TiM-C and TiM-R interventions and ensure they meet the needs of end users.

A mixture of individual and group interviews will be used to collect the data, based on participant preference. Purposive sampling will recruit approximately 25-35 participants for this WP (approximately 5-to-7 per user group) across 5 sites. In line with the INCLUDE study [18], methods will be used to recruit those who do not usually engage in research and include a range of demographics (eg, age, gender, and ethnicity), clinical characteristics (eg, duration and severity of MND), and levels of experience with technology to support access to health care and research. We will not set specific numbers we will recruit for each of these categories, but will continually assess our inclusivity throughout recruitment to ensure we are not excluding any group. Interviews will be conducted either face-to-face or using videoconferencing software. The interviews will last approximately 30-60 minutes in duration and be conducted by members of the research team.

All interviews will begin with simple introductory questions to ask the participants about their experience with MND (either having, supporting, or researching MND). Group interviews will also begin with introductions between the various group participants. After the introduction, specific questions will depend on which user group the participant belongs to.

For people with MND and caregivers, questions will relate to what needs they have that are currently not being met and how TiM-C may be developed to meet these needs. Further questions will relate to how they feel about engaging in remote research (eg, consenting, data collection, and building trust through TiM), and any specific developments they believe TiM-R should include.

For HCPs, questions will be asked about how they use TiM-C, elicit unmet needs within their services, what aspects are required to provide good quality care, and how TiM-C could be further developed to help provide these. Questions will also be included relating to the TiM-R development and how this will interact with TiM-C.

For MND researchers and industry, questions will focus on the current difficulties with conducting research within MND, what is required to deliver good-quality research studies, and how TiM-R can incorporate those functions to facilitate the conduct of remote research and large-scale clinical trials.

Interviews will be audio-recorded and transcribed verbatim for analysis. All identifiable information will be removed during transcription with a pseudonym replacing the participant’s name. Participants will have the option to choose their own pseudonyms. The research team will conduct a framework analysis using NVivo [21]. The analysis will focus on semantic (as opposed to latent) meanings within the transcripts. Findings from the analysis will be provided to an intervention development team, consisting of multiple different stakeholders, and used to further develop the TiM-C and TiM-R systems. After developments have been implemented, the intervention development team will then decide whether to conduct an additional round of interviews, using the same methodology described above. These interviews may use the same individuals who participated in the first round.

